## Abstract

**Background:**

Lithium has proven suicide preventing effects in the long-term treatment of patients with affective disorders. Clinical evidence from case reports indicate that this effect may occur early on at the beginning of lithium treatment. The impact of lithium treatment on acute suicidal thoughts and/or behavior has not been systematically studied in a controlled trial. The primary objective of this confirmatory study is to determine the association between lithium therapy and acute suicidal ideation and/or suicidal behavior in inpatients with a major depressive episode (MDE, unipolar and bipolar disorder according to DSM IV criteria). The specific aim is to test the hypothesis that lithium plus treatment as usual (TAU), compared to placebo plus TAU, results in a significantly greater decrease in suicidal ideation and/or behavior over 5 weeks in inpatients with MDE.

**Methods/Design:**

We initiated a randomized, placebo-controlled multicenter trial. Patients with the diagnosis of a moderate to severe depressive episode and suicidal thoughts and/or suicidal behavior measured with the Sheehan-Suicidality-Tracking Scale (S-STS) will be randomly allocated to add lithium or placebo to their treatment as usual. Change in the clinician administered S-STS from the initial to the final visit will be the primary outcome.

**Discussion:**

There is an urgent need to identify treatments that will acutely decrease suicidal ideation and/or suicidal behavior. The results of this study will demonstrate whether lithium reduces suicidal ideation and behavior within the first 5 weeks of treatment.

**Trial registration:**

ClinicalTrials.gov identifier: NCT02039479

## Background

Over the past several decades our knowledge about suicidal behavior has greatly increased. Research could prove the importance of the interplay between neurobiological, social, psychological, cultural and environmental factors for the development of suicidal behavior. Epidemiological studies have led to more information about risk and protective factors in general population and in patients with psychiatric diseases. As it is indicated in the first report on suicide prevention (WHO 2014 [1]) many universal, selected and indicated strategies have been implemented worldwide to improve the knowledge about suicide, increase the access to health care professionals, train the gatekeepers and therefore lead to an improvement in identification and management of people at risk. Twenty eight countries have established national suicide prevention programs dedicated to suicide research and prevention; however, there is still a need to expand suicide prevention research and anti-suicidal strategies. Lithium treatment has been a popular research avenue given its often replicated anti-suicidal effects and different effects on the human body.

For example, studies have investigated the influence of lithium therapy on neuroprotection [2], inflammation [3], genetic changes [4] and its anti-suicidal properties. Lithium is approved in International Guidelines for the maintenance treatment of bipolar disorder [5–7] and has shown to be effective in prevention of depressive and manic episodes. Long-term treatment with lithium has been shown to be effective in preventing both suicide and attempted suicide in patients with unipolar and bipolar depression. Further, lithium appears to be more effective in reducing suicide compared to other pharmacological treatments effective in preventing mood episodes (e.g. valproate) as well as compared to placebo. One piece of evidence derives from randomized controlled trials investigating the mood-stabilizing effect of lithium. More specific information, however, has been gained from the careful analysis of cohorts of well documented patients having received lithium over many years under constant systematic monitoring (for a comprehensive overview please see Lewitzka et al., submitted [8]). As patients with mood disorders have a 30-fold greater risk of suicide compared to the general population, it is of great importance to systematically study the acute effects of lithium in a controlled setting.

So far little is known about the mechanism behind this effect. Neurobiological research has focused on lithium’s influence on neurotransmitters such as serotonin [9] or noradrenalin and dopamine [10]. Lithium’s influences on the cortisol stress hormone system [11], the γ-aminobutyric-acid [12], second messenger systems such as the inositol metabolism and glycogen synthase kinase 3 have also been investigated [13]. Lithium has demonstrated to have an effect on impulsivity and aggression via several pathways within the nerve cell [14, 15] which is discussed as one of the underlying mechanisms behind the anti-suicidal efficacy.

As suicide research has to deal with specific methodological difficulties the design and development of study protocols needs to be cautious. Ethical and statistical issues need thoughtful consideration.

In 2005, the worldwide first placebo-controlled randomized trial designed specifically to investigate the influence of lithium on suicidal behavior was conducted and published in 2008 by Lauterbach et al. [16]. Survival analysis showed no significant difference in suicidal acts between lithium and placebo-treated individuals (adjusted hazard ratio 0.517; 95 % CI 0.18–1.43); however, post hoc analysis revealed that all completed suicides had occurred in the placebo group accounting for a significant difference in incidence rates (*P* = 0.049). Within a treatment period of one year, no suicides occurred within the lithium group (*n* = 84) compared to three suicides within the placebo group (*n* = 83). No significant differences were found in terms of suicide attempts (seven suicide attempts each in the placebo and lithium group). To date, no study has investigated how fast this anti-suicidal effect appears. It is unclear where in the course of treatment this effect arises.

The primary aim of the present study is to determine whether lithium exerts an anti-suicidal effect through a decrease in suicidal thoughts and/or behavior within the first 5 weeks of treatment. The secondary aim of the study is to determine whether lithium influences suicidal thoughts and/or behavior through the indirect path of improving depressive symptoms, anxiety or impulsivity.

### Methods/Design

The present study is a multi-center, 4 year, randomized placebo-controlled double-blind trial. Patients with unipolar or bipolar disorder suffering from a major depressive episode with suicidal thoughts and/or behavior according to DSM IV criteria will be randomly allocated to lithium therapy plus treatment as usual versus placebo treatment plus treatment as usual. The hypothesis to be tested is that lithium treatment plus treatment as usual leads to a significant reduction of suicidal thoughts and/or behavior compared to placebo therapy plus treatment as usual within 5 weeks of treatment. The primary end point of this study is the change in Sheehan Suicidality Tracking Scale (S-STS, [17]) between the beginning of treatment and after a treatment episode of 5 weeks. Further endpoint in this study are changes in the Columbia-Suicide Severity Rating Scale (C-SSRS, [18]), the Montgomery Asberg Depression Rating Scale (MADRS, [19]), the Hamilton Anxiety Scale (HAM-A, [20]), the Clinical Global Impression Scale (CGI, [21]) and the Barratt Impulsivity Scale (BIS, [22]) from initial treatment to 5 weeks post treatment. A comparison of total scores in the C-SSRS, MADRS, HAM-A and the Young Mania Rating Scale (YMRS, [23]) within the participating centers will be conducted. In addition, the number and dosage of concurrent medication and number of psychotherapy hours will be explored as secondary endpoint. Weekly changes in the C-SSRS, MADRS, HAM-A and YMRS within the observation period and percentage of days where the S-STS Scale score equals zero will be reported. Two-hundred and fifty-four patients will be included with, thereof 127 in each treatment group. Recruitment started on October first, 2013 and will end on September 30^th^, 2017. Treatment includes 5 weeks of treatment plus 1 week of follow-up. For a detailed description of the inclusion and exclusion criteria, please see Table 1.

**Table 1 Tab1:** In-and exclusion criteria

Inclusion criteria	Exclusion criteria
- Male and female patients at least 18 years of age and older - Presenting with a depressive episode (MDE, uni/bipolar), moderate to severe according to DSM IV criteria - Admitted as an inpatient - Suicidal thoughts and/or behavior defined by a score ≥ 8 in the S-STS scale and a score ≥ 20 in the MADRS Scale at time of screening and baseline - Written informed consent	- Pre-treatment with lithium within the last six months before inclusion in the study - Patients after compulsory hospitalization or patients unable to understand the study protocol - Diagnosis of antisocial and/or Borderline personality disorder, alcohol and drug dependency (positive drug screening) - Contraindication following drug approval such as severe heart failure (arrhythmias), severe renal dysfunction, Addison’s disease and others - History of hypersensitivity towards components of trial medication - Pregnant or lactating women, women attempting to get pregnant, and women not practicing a reliable method of contraception

### Study population

Patients will be recruited from six psychiatric hospitals (Dresden University Clinic, Dresden Neustadt, Berlin, Bochum, Frankfurt, Göttingen) in Germany. Specifically, patients will be recruited upon admission. All patients meeting inclusion criteria will be informed about the study by one of the investigators. Following informed written consent, randomization will be conducted by a central block design, allocating the participant to one of the two treatment groups. Figure 1 shows the trial time-line.

**Fig. 1 Fig1:**
[figure not shown]
Trial flow

### Intervention/Course

Patients allocated to the lithium treatment group will receive an oral starting dose of 295 mg lithium carbonate on the first day, increased to 885 mg on the second day, increasing the dosage to serum concentrations between 0,6 and 1,0 mmol/l regularly given twice daily for a total of 5 weeks. Lithium levels will be measured 3 days after first intake and every 3 days after dose changes. Those being allocated to the placebo group will receive the placebo with a virtual concentration level between 0,6 and 1,0 mmol/l also for 5 weeks. The psychiatrist who dispenses and recommends dose adjustments of both lithium and placebo will be different from the patient’s treating psychiatrist and will be blind to the patients study group. Both groups will receive treatment as usual for their depressive symptoms. The average hospital stay for patients with depression and suicidal thoughts and/or behavior in Germany is about 4 weeks. If the patient is discharged from the hospital before the end of the study, the patient will continue in the study as an outpatient using the same procedure.

In total there will be nine study visits. The screening visit (V1, day −3 to 0) will involve confirmation of eligibility, informed written consent, anamnesis, an ECG, a physical exam, and a blood sample for lithium level measurement. Afterwards (up to 3 days later) a baseline screening visit (V2) at day 0 will occur. At the baseline visit, eligibility will be re-confirmed in addition to randomization and beginning of treatment in the evening. Three days after the baseline visit (V2), weekly visits (V3–V7) will occur involving psychometric testing, examination of vital signs and concurrent medication. Any adverse events as well as lithium levels will be carefully documented at each visit. The end of treatment will be on the day of the last weekly visit (V8). Within 1 week following visit 8 will be the final follow-up visit. This visit will involve safety measurements such as vital signs, ECG and a blood sample.

### Assessments

#### Clinician administered scales

The Mini International Neuropsychiatric Interview (MINI, [24]) as well as the structured clinical interview for DSM-IV axis II personality disorders (SKID II, [25]) will be used for diagnosis. To assess suicidal thoughts and/or behavior, the Sheehan Suicidality Tracking Scale (S-STS) is used, both as clinician and self-reported. The S-STS scale was selected because it maps directly to the Columbia Classification Algorithm of Suicide Assessment (C-CASA) coding system, endorsed by the FDA. The S-STS evolved from the Suicidality Module of the MINI Structured Diagnostic Interview for DSM-IV and is a prospective self or clinician report scale. The eight item scale assesses treatment-emergent suicidal ideations and treatment-emergent suicidal behaviors. Each item of the S-STS is scored on a 5-point Likert scale (0 = not at all, 1 = a little, 2 = moderately, 3 = very, and 4 = extremely) and it takes approximately 1 to 2 min to complete. Data from the Sheehan-STS can be analyzed as individual item scores, suicidal ideation subscale score, suicidal behavior subscale score, and total score.

As suicidal thoughts and/or behavior are primary outcomes in this study we also included the Columbia-Suicide Severity Rating Scale (C-SSRS) which has demonstrated good convergent and divergent validity with other multi-informant suicidal ideation and behavior scales and demonstrates high sensitivity and specificity for suicidal behavior classifications. The C-SSRS distinguishes between the domains of suicidal ideation and suicidal behavior. Four constructs are measured. The first is the severity of ideation, which is rated on a 5-point ordinal scale in which 1 = wish to be dead, 2 = nonspecific active suicidal thoughts, 3 = suicidal thoughts with methods, 4 = suicidal intent, and 5 = suicidal intent with plan. The second is the intensity of ideation subscale, which comprises 5 items, each rated on a 5-point ordinal scale: frequency, duration, controllability, deterrents, and reason for ideation. The third is the behavior subscale, which is rated on a nominal scale that includes actual, aborted, and interrupted attempts; preparatory behavior; and non-suicidal self-injurious behavior. The fourth subscale describes lethality, containing the assessment of actual attempts and actual lethality. It is rated on a 6-point ordinal scale, and if actual lethality is zero, potential lethality of attempts is rated on a 3-point ordinal scale. The C-SSRS is frequently recommended by various international agencies such as the FDA or WHO.

The Montgomery Asberg Depression Rating Scale (MADRS) and the Hamilton Anxiety Rating Scale (HAM-A) assess depressive and anxiety symptoms. Symptom severity, treatment response and the efficacy of treatment are measured using the Clinical Global impression scale (CGI).

#### Patient administered scales

To investigate whether the psychological construct of impulsivity is associated with suicidality, the Barratt Impulsiveness Scale (BIS) will be applied at weekly intervals during the study. The BIS is a widely used measure of impulsiveness and includes 30 items that are scored to yield six first-order factors (attention, motor, self-control, cognitive complexity, perseverance and cognitive instability impulsiveness) and three second-order factors (attentional, motor, and non-planning impulsiveness). The patients will be also asked to fill out the S-STS as a self-rating instrument on a daily basis.

### Power analysis and sample size calculation

A comparable study published by Khan et al. [26] of a 6-week double-blind trial in 40 patients found a score reduction of 4.8 (SD = 5.1) in the clinician administered S-STS in the placebo group, while a score reduction of 6.7 (SD = 5.8) was found among the lithium group The assumption that all lithium patients achieve a therapeutic serum-level in the current study seems to be reasonable due to the considerable higher lithium dose in comparison with the Khan et al. study. Therefore, these values have been used as estimates for the expected group difference in this study.

With an alpha level of 0.05, and statistical power of 0.8, sample size estimation for a two-sided *t*-test with unequal variances results in a required number of 131 patients per group. Nevertheless, a *t*-test has considerably less power than an analysis of covariance (ANCOVA), which will be used in this analysis. Borm et al. [27] showed for sample size n and a baseline-follow-up correlation rho, that an ANCOVA with (1-rho^2)*n subjects has the same power as the corresponding *t*-test. There is no published data on test-retest correlations of the S-STS to our knowledge; however, a recalculation of data from the “Basis-Studie Kompetenznetz Depression” [28] with 1014 naturalistically treated depressed patients showed correlations from 0.36 to 0.54 for the self-report S-STS between baseline and week 8. Therefore, a conservative assumption of 0.3 for the expected correlation was chosen, which yields a number of 120 patients per group. These patients will form the modified Intention to Treat (ITT) sample including all patients who will be randomized and not discontinue from the study before any efficacy measurement. A rate of approximately 5 % of randomized patients dropping out for any reason before entering the ITT sample is presumed, which results in 127 patients needed to be randomized per group. Therefore, 508 patients will be required to be screened assuming a rate of 50 % of screened patients fulfilling the inclusion criteria. We are expecting good adherence to the intervention as this will not result in major side effects. However, we anticipate that there will be about 5 % loss to follow-up, and this is accounted for in the sample size estimation.

As the study is a multi-center trial, randomization will be carried out by a centralized computer randomization directly after screening and obtainment of written informed consent at visit 2 (baseline). Study participants and the treating mental health team on the inpatient unit will be blinded for group assignment. A rater-training (including assessment of inter-rater reliability) will be provided before the study commences to minimize differences between centers.

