### Statistical analysis

Descriptive statistics using proportions, means and standard deviations will be reported where appropriate. All efficacy outcome measures will be analyzed on an intent-to-treat (last observation carried forward) basis and study completer basis. Results will be presented with 95 % confidence intervals where applicable. Proportions of adverse events will be summarized. All statistical tests will be two-sided using an alpha level of 0.05. Analyses will be adjusted for age and gender when there is a significant difference between the groups at baseline.

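### The (1-rho²) ANCOVA reduction is applied to a sample size built on SDs of change, so 120 per group for 80% power does not follow from the stated inputs and calling rho = 0.3 conservative is unsupported

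*Protocol article*

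**What the plan says.** All the inputs stand in the section on power analysis and sample size calculation of the protocol article. The planning values come from a cited 6-week study with 40 participants. For its control arm, the article reports that the study "found a score reduction of 4.8 (SD = 5.1) in the clinician administered S-STS in the placebo group". The figures for the active arm follow in the same sentence: 6.7, with an SD of 5.8. On their use, the article adds that "these values have been used as estimates for the expected group difference in this study". The error rates are an alpha of 0.05, two-sided, and a power of 0.8. A t-test that allows unequal variances then leads to a "required number of 131 patients per group".

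The article then turns to the planned ANCOVA. It cites a published result, with rho the correlation between baseline and follow-up: "an ANCOVA with (1-rho^2)*n subjects has the same power as the corresponding" (the comparator being the t-test). It reports correlations of 0.36 to 0.54 for the self-report S-STS in another cohort, and concludes: "a conservative assumption of 0.3 for the expected correlation was chosen, which yields a number of 120 patients per group". Allowing for 5% loss before the modified ITT sample gives 127 randomised per group.

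Under the primary outcome heading, the model is an ANCOVA of the final clinician-rated S-STS score with the initial score as covariate.

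**The concern.** The SDs 5.1 and 5.8 describe score reductions, so the t-test behind 131 is a test on change scores. The factor (1-rho²) is the ratio of the ANCOVA residual variance to the variance of the final score. It converts the sample size of a t-test on final scores, and no SD of final scores is given. Applied to a change-score sample size, it mixes two variances.

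Two statements depend on this step: that 120 analysed patients per group give 80% power, and that a correlation of 0.3 errs on the safe side. If recruitment runs slow, it matters whether 80% power needs nearer 86 or nearer 131 per group, and the article does not settle that.

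**Working it through.** **Inputs.** Difference 6.7 - 4.8 = 1.9; SDs of change 5.1 and 5.8; two-sided alpha 0.05; power 0.80; rho 0.3 (assumed), 0.36 and 0.54 (reported). All are from the sample size section; two-sidedness is repeated in the statistical analysis section. The ratio k = baseline SD/final SD is not given, so a range is shown.

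**1. The plan's own figures reproduce.** A Welch t-test (noncentral t) with these inputs has 79.8% power at 130 per group and 80.1% at 131. Then 131 × (1 - 0.3²) = 131 × 0.91 = 119.2, rounded up to 120, and 120/0.95 = 126.3, rounded up to 127. The arithmetic is correct; the choice of factor is the issue.

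**2. The matching factor.** Write s0 and s1 for the baseline and final SDs.

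- Variance of change: s0² + s1² - 2·rho·s0·s1
- ANCOVA residual variance: (1 - rho²)·s1²
- Ratio, with k = s0/s1: F = (1 - rho²)/(1 + k² - 2·rho·k)

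F equals (1 - rho²) only if 1 + k² - 2·rho·k = 1, that is k = 2·rho: 0.6 at rho 0.3, 0.72 at 0.36 and 1.08 at 0.54. With equal SDs (k = 1), F reduces to (1 + rho)/2.

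**3. Bound.** F can be rewritten as 1 - (k - rho)²/(1 + k² - 2·rho·k). It never exceeds 1 and reaches 1 at k = rho. So at most 131 per group are needed, and power at 120 is never below that of the change-score t-test at 120, which is 76.5%.

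**4. Results.** Required n is 131·F rounded up. Power at 120 is the Welch power with both variances multiplied by F.

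| k | rho 0.3: F, n, power | rho 0.36: F, n, power | rho 0.54: F, n, power |
|---|---|---|---|
| 0.3 | 1.000, 131, 77% | 0.996, 131, 77% | 0.925, 122, 80% |
| 0.4 | 0.989, 130, 77% | 0.998, 131, 77% | 0.973, 128, 78% |
| 0.5 | 0.958, 126, 78% | 0.978, 129, 77% | 0.998, 131, 77% |
| 0.6 | 0.910, 120, 80% | 0.938, 123, 79% | 0.995, 131, 77% |
| 0.8 | 0.784, 103, 86% | 0.818, 108, 84% | 0.913, 120, 80% |
| 1 | 0.650, 86, 91% | 0.680, 90, 90% | 0.770, 101, 86% |
| 1.25 | 0.502, 66, 97% | 0.524, 69, 96% | 0.584, 77, 94% |

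Simulating the ANCOVA with equal SDs and 120 per group gave 91% power at rho 0.3 and 87% at rho 0.54, in line with the table.

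**5. Direction in rho.** The derivative of F with respect to rho has the sign of (k - rho)·(1 - rho·k), which is the sign of k - rho for the values considered here. Below k, a smaller rho lowers the required n. For k of 0.5 and above in the table, rho 0.3 gives the smallest n of the three correlations. At k = 0.3 the order turns round (131 at rho 0.3, 122 at rho 0.54), and at k = 0.4 rho 0.3 needs 130 against 128 at 0.54. Under the plan's formula a smaller rho always raises n (120 at 0.3, 115 at 0.36, 93 at 0.54), which is why 0.3 looks cautious there.

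**The case against.** Much can be said for the plan. Its arithmetic is right throughout. The entry rule in Table 1 (S-STS of at least 8 at screening and baseline) may narrow the baseline distribution, so k below 1 is plausible and the equal-SD figures should not be read as the expected case. The same restriction tends to lower the correlation. The reported 0.36 to 0.54 also come from the self-report scale in naturalistically treated patients, so assuming a value below that range has a rationale. The error is bounded: the worst case is about 3.5 points under the 80% target. A null result would be read mainly from the 95% confidence interval that the article promises. All of this stands, and it limits the point to the derivation and its wording.

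It does not rescue the step from 131 to 120, because the article neither states nor argues for the SD ratio that the step needs.

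Three stronger readings are tempting and are not supported:

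- **That 120 per group misses 80% power.** Without k this cannot be shown. About 80% is reached at rho 0.3 with k = 0.6, at rho 0.36 with k about 0.65, and at rho 0.54 with k about 0.8.
- **That the trial is underpowered, or that it is oversized.** Either can be true, depending on k.
- **That 0.3 is always the optimistic choice.** That holds only while rho is below k. Nor is 0.3 one end of the reported correlations; it lies below them.

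**Conclusion.** The point holds as a mismatch between the factor and the SDs it is applied to. The stated inputs do not determine the ANCOVA sample size, so the claim that 120 per group gives 80% power is unsupported rather than shown to be false. For rho from 0.3 to 0.54 and k from 0.4 to 1, power at 120 runs from about 77% to 91%. It is higher still if the baseline SD exceeds the final SD, and never below about 76.5%. The description of 0.3 as conservative has no basis unless k is known to be small.

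These figures assume a true difference of 1.9, the change-score SDs as stated, and the same rho and k in both arms. The range of k is an assumption made for this check. The algebra is certain; the direction and size of the power error are not. The correction is worth making because the trial is described as confirmatory, but it does not call the design into question.

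**What to change.** Keep 127 randomised per group. In the sample size section, delete the word conservative and the (1-rho²) step on the change-score SDs. Then do one of two things:

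- State the SD of the final clinician-rated S-STS score with its source, run the t-test calculation on that SD, and apply (1-rho²) to the result.
- Keep the change-score SDs and report ANCOVA power at 120 per group with F = (1-rho²)/(1+k²-2·rho·k), over rho from 0.3 to 0.54 and a range of k declared as an assumption. For k from 0.4 to 1 this is about 77% to 91%, with a floor of about 76.5%.

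If the baseline and final SDs are available from the cited trial or the correlation cohort, they should replace the assumed range. The cost is one rewritten paragraph; enrolment and the primary analysis stay as they are.
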